## Abstract

**Background:**

Access to long-lasting insecticidal nets (LLINs) has increased and malaria has decreased globally, but malaria transmission remains high in parts of sub-Saharan Africa and insecticide resistance threatens current progress. Eave tubes are a new tool for the targeted delivery of insecticides against mosquitoes attempting to enter houses. The primary objective of this trial is to test whether screening plus eave tubes (SET) provides protection against malaria, on top of universal coverage with LLINs in an area of intense pyrethroid resistance. The trial will also assess acceptability and cost-effectiveness of the intervention.

**Methods/design:**

A two-armed, cluster randomized controlled trial will be conducted to evaluate the effect of SET on clinical malaria incidence in children living in central Côte d’Ivoire. Forty villages will be selected based on population size and the proportion of houses suitable for modification with SET. Using restricted randomization, half the villages will be assigned to the treatment arm (SET + LLINs) and the remainder will be assigned to the control arm (LLINs only). In both arms, LLINs will be distributed and in the treatment arm, householders will be offered SET.

Fifty children aged six months to eight years old will be enrolled from randomly selected households in each of the 40 villages. Cohorts will be cleared of malaria parasites at the start of the study and one year after recruitment, and will be monitored for clinical malaria case incidence by active case detection over two years. Mosquito densities will be assessed using CDC light traps and human landing catches and a subset of *Anopheles* mosquitoes will be examined for parity status and tested for sporozoite infection.

Acceptability of SET will be monitored using surveys and focus groups. Cost-effectiveness analysis will measure the incremental cost per case averted and per disability-adjusted life year (DALY) averted of adding SET to LLINs. Economic and financial costs will be estimated from societal and provider perspective using standard economic evaluation methods.

**Discussion:**

This study will be the first evaluation of the epidemiological impact of SET. Trial findings will show whether SET is a viable, cost-effective technology for malaria control in Côte d’Ivoire and possibly elsewhere.

**Trial registration:**

ISRCTN18145556, registered on 01 February 2017 – retrospectively registered.

## Background

The incidence of malaria worldwide declined by 41% between 2000 and 2015 [1, 2]. Malaria vector control tools, primarily long-lasting insecticidal nets (LLINs) and indoor residual spraying (IRS), have been instrumental in reducing the global disease burden [2]. Maintaining and extending this progress requires innovative, cost-effective vector control methods to overcome challenges including remaining areas of high transmission, increasing levels of insecticide resistance in vector populations, and operational and financing constraints on LLIN and IRS [3–8].

Although house modifications to prevent mosquito entry are not a new malaria control tool [9, 10], there is recent renewed interest in improved housing - such as replacing thatch roofs with metal, screening windows, and closing eaves (i.e., the gap between the top of the wall and the roof) - for the purpose of malaria control [11]. An ongoing randomized controlled trial (RCT) in the Gambia is testing the epidemiological and entomological impact of replacing thatch roofs with metal, and screening open eaves, windows and doors, in addition to the current best practice of LLINs [12]. Another RCT carried out in the same region found a 22% reduction in the number of malaria vectors (*Anopheles gambiae* mosquitoes) captured indoors, and a 7% reduction in anemia in children living in houses with screening and closed eaves, compared to unmodified houses [13]. A recent detailed analysis of survey data from 21 countries throughout sub-Saharan Africa found a significant inverse association between “modern” house traits and reduced malaria prevalence in children, on par with the protection provided by insecticide treated bednets [14].

Open eaves, which are found in many traditional African houses, are a particularly important source of attractive cues for malaria mosquitoes, and represent the key entry point for *An. gambiae* in sub-Saharan Africa [15–18]. It was this aspect of mosquito behavior that motivated the initial development of eave tubes [19–22]. Eave tubes provide targeted insecticide treatment and, in combination with “mosquito proofing” of the house (screening windows, closing eaves and sealing any other cracks or openings), reduce mosquito entry into the house while still maintaining airflow through the eaves. Relying on cues that typically draw malaria mosquitoes into houses, eave tubes turn the house into what is effectively a “lure and kill” device.

The eave tube consists of a section of pipe fitted into a closed eave, with a screened insert that is placed inside the tube. The insert is treated with an electrostatic coating, which holds powder formulations of insecticides. This insecticide delivery method can be highly effective, even against resistant mosquitoes [23]. Killing mosquitoes as they attempt to enter houses via the eave tubes offers potential for community level impact, similar to that observed with insecticide treated bednets, if the coverage of the technology is high [19]. The screening component, which physically reduces mosquito entry into the house, offers passive protection for every person sleeping inside the house, regardless of whether they are under a bednet.

The aim of the cluster randomized controlled trial (CRT) presented here is to determine whether screening plus eave tubes, the SET intervention, provides protection against malaria, on top of the current best practice of universal coverage of LLINs (one bednet per two people). LLINs are the primary tool used for malaria vector control globally [1] and therefore the trial is designed to reveal any benefits from SET on top of standard control measures. The trial will be based in central Côte d’Ivoire, where there is intense insecticide resistance [24], to evaluate the efficacy, acceptability, and cost-effectiveness of the intervention in an area where existing vector control tools may be compromised by resistance.

## Study objectives

### Epidemiology

#### Primary objective

To assess whether SET (screening plus eave tubes) and LLINs (at universal coverage) reduces the incidence of clinical malaria in children between the ages of six months and ten years, compared to universal coverage of LLINs alone.

#### Secondary objectives

Assess whether SET + LLINs reduces the incidence of malaria infection in children between the ages of six months and ten years, compared to LLINs alone.Assess whether SET + LLINs reduces the prevalence of anemia in children between the ages of six months and five years, compared to LLINs alone.Assess whether SET + LLINs is associated with a rise in symptoms of respiratory infections in children between the ages of six months and ten years, compared to LLINs alone.

### Entomology

#### Primary objective

Assess the impact of SET + LLINs on indoor and outdoor densities of malaria vectors, compared to LLINs alone.

#### Secondary objectives

Assess the impact of SET + LLINs on entomological inoculation rate (EIR; mean number of sporozoite infective bites/person/year), compared to LLINs alone.Assess the impact of SET + LLINs on parity in the malaria vector population, compared to LLINs alone.Monitor levels of insecticide resistance in villages that receive SET + LLINs, compared to villages that receive LLINs alone.

### Social science

#### Primary objective

Assess end users’ perceptions of and willingness to adopt SET in the treatment and control arms, and predictors of those perceptions and actions.

#### Secondary objectives

Assess malaria prevention behavior in households with SET versus LLINs alone, as well as within the treatment and control arms.Assess willingness to maintain SET and identified key factors that influence willingness to maintain.Measure attitudes, emotions, knowledge, and beliefs relating to malaria and malaria control interventions, including SET and LLINs.

### Economics

#### Primary objective

Measure the incremental cost-effectiveness of adding SET to LLINs from the societal and provider perspective under trial conditions.

#### Secondary objectives

Establish the relative contribution to costs of the distinct programmatic elements (house modifications, installation of the eave tubes, treatment and retreatment of the eave tube inserts with insecticides, and maintenance of the housing repairs and eave tubes), and identify the inputs that contribute the most to overall costs.Estimate the potential cost of providing SET at larger scale over an extended period of 3 and 5 years under operational scenarios.

## Methods/design

### Study area

The study site is situated in the Gbêkê region in central Côte d’Ivoire. It is highly malaria endemic with year-round transmission, peaking during the rainy season (May through October) [25–27]. Forty candidate villages have been identified within a 60 km radius around the town of Bouaké (Fig. 1). Selection criteria for these candidate villages were: between 100 to 600 houses, at least 80% of houses suitable for installation of the SET intervention (i.e. roofs made out of metal sheeting and walls made out of concrete or brick), and villages at least 2 km from any other candidate study village.

**Fig. 1 Fig1:**
[figure not shown]
Map of study area and 40 candidate study villages

### Participant recruitment

Community consent to participate in the study will be obtained through meetings with village leaders and inhabitants. A census will be carried out prior to the start of the study. LLIN distribution numbers will be calculated based on data from the census. Consent for the house modifications will be obtained from individual homeowners during door-to-door visits, following the randomization of villages to trial arms.

Each candidate village is associated with a health center that is responsible for providing medical care to a group of villages. In cases where the health center is not situated in the village, a Community Health Worker (CHW) is charged with providing routine care for uncomplicated malaria, diarrhea, and mild respiratory infections in children. Study team members will visit each of the health centers associated with a trial village, to inform the health center officials of the trial activities. CHWs in the trial villages will be trained in the trial procedures.

Eligible children will be randomly selected for recruitment into the active case detection (ACD) cohort in each village. Recruitment will be limited to children aged eight or younger, to avoid children aging out during the two year monitoring period. Study team members will seek informed consent from the parents or caregivers of the children before enrolling the child in the cohort. Children aged eight will be asked to assent, in addition to parental consent. Children in the treatment arm will be recruited for the cohort irrespective of whether they live in a house that has been modified with SET to avoid bias related to house structure.

### Study design

The study design is summarized in Fig. 2 and a schedule of trial activities is presented in Table 1. The design is a two-armed CRT with 20 villages (clusters) per arm. Villages will be allocated to an arm through restricted randomization. Villages in the control arm will receive universal coverage of LLINs, while the villages in the treatment arm will receive universal coverage of LLINs and heads of household living in suitable houses will also be offered the SET intervention free of charge. The target coverage for SET in the treatment arm is ≥65% of all houses in the village. After the installation of SET (in the treatment arm) and the distribution of LLINs (in both arms), the epidemiological and entomological monitoring will begin.

**Fig. 2 Fig2:**
[figure not shown]
Summary of study design

**Table 1 Tab1:**
[figure not shown]
Timetable of trial activities

During the first visit and one year after recruitment, all children in the ACD cohort will be cleared of malarial parasites. Children in the cohort will be monitored for two years to determine clinical malaria incidence, malaria infection incidence, and prevalence of acute respiratory infections. Twice a year, at the start and end of the rainy season, all children in the cohort aged five years or younger will be tested for anemia. If the child leaves the village permanently or the parents withdraw their consent, another child will be recruited into the cohort, preferably of similar age and in the same household.

Indoor mosquito density will be monitored every other month in 12 randomly selected houses in each village using CDC light traps. Indoor and outdoor mosquito density and exposure to infectious bites will be assessed using human landing catches (HLC) every month in four randomly selected houses per village. Four villages in each study arm will be selected for insecticide resistance monitoring. The villages will be selected based on the presence of permanent breeding sites. Mosquitoes from these eight villages will be sampled once a year over four years (once before the start of the study, once each year of the study, and once after the end of the study).

Questionnaires will be administered to consenting participants in six study villages (three in each trial arm) at the start and end of the monitoring period, and in two study villages (one in each trial arm) at the midpoint of the monitoring period. Ethnographic studies will take place in three of the villages in the trial arm during the installation of the SET intervention. Focus groups also will be conducted midway through the trial in two villages from the treatment arm and one village from the control arm. Data from the social science activities will inform the economic evaluation, but no primary cost data will be collected from households.

### Randomization and blinding

Allocation of villages to study arms will be restricted to randomizations that limit the difference between the mean values in each study arm of the following: malaria prevalence; socioeconomic status; village size, and proportion of houses suitable for SET. Data on these variables by cluster will be obtained through a pre-trial cross-sectional survey. Data on any additional potentially confounding ecological factors not included in the randomization will be collected and corrected for in the analysis.

Given the nature of the intervention, it is impossible to conduct this study in a fully blinded manner but those parts of the data collection that can be blinded will be. Observer bias will be reduced where feasible. All laboratory work with samples will be blinded where possible. Standard light traps that do not rely on the ability of the fieldworker to collect specimens will be used to reduce mosquito collector bias, in addition to HLCs. All analyses will be conducted on blinded data.

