## Sample size rationale

### Epidemiological

The epidemiological impact of SET alone or in combination with LLINs is currently unknown. A minimum effect size of 40% was used in the sample size calculations, which is similar to the effect size used in other sample size calculations for house-based malaria interventions [12, 35]. The mean incidence of clinical malaria in the reference arm was assumed to be 0.5 malaria cases per child per year, based on existing data from the study area. Further assuming a coefficient of variation (k) of 0.5, (a conservative estimate for a high transmission setting), 80% power and significance level of 5%, requires 20 clusters per arm and 50 children per cluster to be followed for two years (encompassing 2 peak transmission seasons).

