## Statistical analysis

### Epidemiological

Protective efficacy against clinical malaria and malaria infection will be determined by comparing incidence rates of malaria infection and clinical malaria between arms. Following any treatment for malaria, a child will not be considered at risk for four weeks and this period will therefore be censored from follow-up. Overnight stays outside of the village will be recorded with a short questionnaire administered during the cohort visits. If travel outside of the village is common, it will be included as a covariate in the analysis.

Primary intention to treat analysis will be comparison of the incidence of clinical malaria episodes in the two intervention groups. All analysis will use a mixed effects model to test the difference in incidence rate between the two arms, allowing for repeated measurements on the same individual, and within-cluster correlation of responses. The effect of year and possible confounders such as age of child, gender, antimalarial drug use, baseline infection status, etc. will be analyzed in separate as per protocol analysis.

Survival analysis will be used to compare time to first infections, adjusting for confounding factors using a Cox proportional hazards model, again using methods that allow for within-village correlation of responses.

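### The plan corrects for village factors outside the restricted randomization but not for the four inside it, so the primary test as written forgoes precision and may be conservative

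*Protocol article*

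**What the plan says.** Under Randomization and blinding, allocations are restricted to those that limit the difference between arm means in "malaria prevalence; socioeconomic status; village size, and proportion of houses suitable for SET". The values will be in hand before allocation: "Data on these variables by cluster will be obtained through a pre-trial cross-sectional survey". The next sentence sets the rule for adjustment: "Data on any additional potentially confounding ecological factors not included in the randomization will be collected and corrected for in the analysis".

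Under Statistical analysis, Epidemiological, the main comparison is described thus: "Primary intention to treat analysis will be comparison of the incidence of clinical malaria episodes in the two intervention groups". The mixed effects model is specified by its correlation structure, "allowing for repeated measurements on the same individual, and within-cluster correlation of responses". Year and possible confounders (age, gender, antimalarial use, baseline infection status and others) "will be analyzed in separate as per protocol analysis". Travel outside the village may enter as a covariate if it proves common, but it is recorded during follow-up and is not a baseline village variable.

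The protocol nowhere places the four restriction variables in the primary model.

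**The concern.** Restricting the allocation on a prognostic variable makes the arms nearly equal on it, so it adds little to the variation of the arm difference. If the model then omits it, its contribution stays in the residual between-village variance. The standard error is then too large for the allocation procedure used: the test rejects too rarely under the null, and some of the precision that the restriction provided is lost.

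The adjustment rule points the other way. It corrects for factors that were not balanced and says nothing of those that were. The word for additional factors implies that the authors regard the four as potentially confounding too, that is, as related to malaria risk. At stake is efficiency in a design whose power is governed by variation between villages.

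**Working it through.** **1. The plan's own figure.** Inputs from Sample size rationale, Epidemiological: control incidence "assumed to be 0.5 malaria cases per child per year"; a 40% reduction, so 0.3 under SET; k = 0.5; 50 children for two years, so y = 100 child-years per village; 80% power; 5% significance, taken as two-sided. From Study design: "The design is a two-armed CRT with 20 villages (clusters) per arm".

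The standard unmatched formula for rates (Hayes and Bennett) is

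c = 1 + (z₁ + z₂)² × [(λ₀ + λ₁)/y + k²(λ₀² + λ₁²)] / (λ₀ − λ₁)²

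= 1 + 7.849 × [0.8/100 + 0.25 × (0.25 + 0.09)] / 0.04

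= 1 + 7.849 × (0.008 + 0.085)/0.04 = 19.25, rounded up to 20.

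Power at 20 per arm is Φ(√(19 × 0.04/0.093) − 1.960) = Φ(0.899) = 81.6%. The stated figure reproduces. The between-village term is 0.085/0.093 = 91% of the variance, so village-level covariates act on nearly all of it.

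**2. Illustrative simulation.** There are 40 villages, lognormal village effects with coefficient of variation 0.5, Poisson counts over 100 child-years, and four village covariates jointly explaining a share R² of between-village variance. Log village rates are compared by a t test, without and with the four covariates. The first eight rows and the last use 4,000 runs per cell (simulation standard error about √(0.05 × 0.95/4000) = 0.3 points at 5%).

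| Restriction assumed | R² | Type I error %, without / with | Power % at 40% effect, without / with |
|---|---|---|---|
| Best-balanced 10% of 200 allocations | 0 | 4.7 / 4.7 | 86.9 / 85.9 |
| same | 0.1 | 4.2 / 4.9 | 88.6 / 89.5 |
| same | 0.3 | 2.5 / 4.7 | 90.0 / 94.4 |
| same | 0.5 | 1.5 / 4.6 | 92.2 / 98.5 |
| Best-balanced 25% | 0 | 4.7 / 4.8 | 87.2 / 85.9 |
| same | 0.1 | 4.2 / 4.5 | 88.9 / 89.5 |
| same | 0.3 | 3.1 / 5.1 | 90.3 / 94.6 |
| same | 0.5 | 1.9 / 4.9 | 91.0 / 98.4 |
| Balance limit 0.25 SD | 0.25 | 3 / 5 | 90 / 94 |
| same | 0.5 | 1 / 4 | 92 / 98 |
| Balance limit 0.5 SD | 0.25 | 4.4 / 4.8 | not shown |
| None (simple randomization) | 0.3 | 5.2 / 5.3 | 88.3 / 92.7 |

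With a single restricted covariate and a 0.5 SD limit, unadjusted type I error is 4.6% at R² = 0.25 and 3.0% at R² = 0.5.

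The simulated power levels are higher than the formula's 81.6% because the test is on the log scale. Only the differences within a row should be read. The last row separates the two effects: without restriction the unadjusted test holds its level, yet adjustment still gains power.

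**3. Smaller effects.** For a 30% reduction with allocation from the best-balanced 10% (2,000 runs), power without and with adjustment is 58% and 61% at R² = 0.1, 59% and 68% at R² = 0.25, and 60% and 82% at R² = 0.5.

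**4. Cost in degrees of freedom.** Two arms of 20 leave 40 − 2 = 38 between-village degrees of freedom. Four covariates leave 34, and the t critical value moves from 2.02 to 2.03.

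**The case against.** The strongest reply is that the article never calls the primary analysis unadjusted. It does not list the model's fixed effects, and a covariate list is commonly left to the analysis plan, which is not shown. The confounders named for separate analysis are child-level or drug-use items; none is a restriction variable. Promising to correct for other factors does not strictly exclude correcting for these four. This stands in part: a reader might infer that the protocol prescribes an unadjusted primary test, and the text does not say so. But it is not silent either. It states which village factors will be corrected for and defines them as those outside the randomization. An analysis plan that followed this wording would leave the four out.

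A second reply is that the size is unknown. This stands in full. The documents give neither the balance limits nor R². With a 0.5 SD limit the conservatism nearly vanishes at R² = 0.25. Eligibility already narrows two of the variables (100 to 600 houses per village, at least 80% of houses suitable), which may reduce what they can explain.

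A third reply is that nothing is invalid. This also stands: any error in the test's level is in the safe direction.

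**Conclusion.** The point holds as one of avoidable inefficiency. As written, the primary test forgoes precision from village data that the pre-trial survey will already have supplied. It is conservative only if the restriction is tight and the variables are prognostic. Across plausible balance limits, type I error is then about 3 to 4.5% at R² = 0.25 and 1 to 4% at R² = 0.5. At the 40% effect, adjustment is worth about 3 to 4 points of power at R² = 0.25 and 5 to 10 at R² = 0.5, next to nothing (about one point) at R² = 0.1, and minus 1 to 2 points at R² = 0. These ranges are somewhat wider than the rows shown because the balance limits are not given. The gain is larger for a 30% effect, which is relevant because the protocol says that the effect of SET is not yet known.

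Two stronger readings are not supported. One is that power would climb from 82% to 90% or 97%. Those figures come from putting k²(1 − R²) into the formula at R² = 0.25 and 0.5, and the 82% starting point gives the restriction no credit; it already raises unadjusted power, so the real gain is smaller. The other is that the trial is underpowered or its test invalid: the 20 clusters per arm reproduce, the stated 80% power stands without adjustment, and type I error is not inflated.

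**What to change.** State in the analysis section that the primary mixed model includes the restriction variables as fixed village-level covariates, pre-trial malaria prevalence at minimum, and report the unadjusted estimate as a sensitivity analysis. Reword the sentence under Randomization and blinding so that it no longer confines correction to factors outside the randomization, and align it with the separate confounder analysis described under Statistical analysis.

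The cost is a sentence or two of text and no new data. Up to four of the 38 between-village degrees of freedom are used, with a loss of 1 to 2 points of power if the variables turn out not to be prognostic. Entering prevalence alone would use one degree of freedom.
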